### Data management and monitoring

The personal data from participants will be handled confidentially, according to Good Clinical Practice guidelines (GCP). Medical history and associated data will be extracted from the electronic patient record. Data will be pseudonymized and stored in a certified online case report form tool (Castor EDC). Personal data that connects the patient to the participant number will be stored by the principal investigator for 15 year according to national guidelines. The study is monitored by the Clinical Trial Center Maastricht (CTCM) in order to assure patient rights and the accuracy of the reported data.

## Discussion

As the number of people affected by Alzheimer’s disease will grow in the upcoming years due to increased life expectancy, there is a need for an accurate, low-invasive and low-cost diagnostic test that could enable early diagnosis. Future therapies combined with earlier diagnosis can increase the chance for preserving cognitive functioning. When people with cognitive complaints are referred to a memory clinic, a biomarker test (PET scan or CSF puncture) is not always chosen, often due to the fact that they are expensive, invasive, or not available. Diagnosis with tear fluid could lower the bar to apply biomarker tests, since it is low-cost and less invasive. Additionally, tear fluid can be collected at the general practitioner where the patient presents first, enabling timely detection. Tear fluid collection also has the potential to be used for screening purposes, due to its minimally invasive nature.

One of the main strengths of our study is the wide range of information that will be available from the participants, ranging from neuropsychological to ophthalmic tests, which will thereby generate a deeply phenotyped cohort. Furthermore, this study combines measurements of tear and retinal biomarkers, which are both low-invasive methods that potentially complement each other. Potential limitations of our study are that participants may be lost for follow-up visits, due to declining to participate, emigration or study drop-out. Particularly patients with fast cognitive decline may be lost somewhere along the two year follow-up. Another limitation is that not all measurements and data will be available for all participants due to different standard procedures and available equipment per study location.

The TearAD study will be the first longitudinal study analyzing tear AD biomarkers in a large cohort. The first results of the TearAD study, expected by early 2025, will inform whether tear AD biomarkers have added value in the screening and diagnosis of AD.

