**Discussion:**

The TearAD study will provide insight into the potential diagnostic use of tear biomarkers as a minimally invasive and low cost tool for the screening and diagnosis of AD.

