## Methods

### Objectives

The primary objective of this study is to evaluate diagnostic accuracy measures of tear biomarkers to discriminate participants with and without neurodegeneration as determined by hippocampal atrophy. The secondary objective is to determine the level of agreement between Aβ and tau protein levels in tear fluid, blood and CSF or PET. Thirdly, we aim to investigate whether the combination of retinal biomarker with tear biomarkers can aid in determining the presence of neurodegeneration as determined by hippocampal atrophy. The final objective is to analyze how biomarkers in tear fluid alter over the course of the follow-up period.

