### Study population

Based on their clinical diagnosis we aim to include 50 patients with SCD, 50 patients with MCI and 50 patients with AD dementia. Additionally, 50 cognitively healthy controls will be included. Eventually, the total study population (*n* = 200) will consist of two groups of 100 participants with signs of neurodegeneration and 100 participants without signs of neurodegeneration. The presence of neurodegeneration will be defined as presence of medial temporal lobe atrophy (MTA) (measured by MRI using visual rating scores of the medial temporal lobes using the Scheltens Visual Rating Method abnormal cutoff of ≥ 2 [22]). The inclusion criteria are described in Tables 1 and 2.

**Table 1 Tab1:** Inclusion criteria for all participants

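### Accuracy is estimated only against visual medial temporal atrophy, while the article promises information on AD diagnosis and analyses its own Aβ-positivity outcome only by correlation of levels

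*Protocol article*

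**What the plan says.** **Target of the conclusion.** The closing paragraph of the Discussion says that the first results "will inform whether tear AD biomarkers have added value in the screening and diagnosis of AD". The Discussion part of the Abstract likewise describes tear markers as a possible "low cost tool for the screening and diagnosis of AD".

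**Reference for accuracy.** Under Objectives, the primary aim is to estimate how well tear markers "discriminate participants with and without neurodegeneration as determined by hippocampal atrophy". Study population and note b to Table 3 define this by the Scheltens visual rating with a cutoff of 2 or more. The Sample size section and the ROC paragraph of Statistical analysis use the same reference. The planned composition is "100 participants with signs of neurodegeneration and 100 participants without signs of neurodegeneration". For the patient groups, "we aim to include 50 patients with SCD, 50 patients with MCI and 50 patients with AD dementia", with 50 healthy controls in addition.

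**AD-specific data.** Outcome measures lists agreement between tear Aβ and Aβ positivity by PET or CSF, separately from agreement of Aβ and tau levels across tear fluid, blood and CSF. Note c to Table 3 makes the status binary: PET is read as positive or negative, and CSF is judged by each clinic's own cut-offs. Both come from subsets whose sizes are not given, and Study design and setting says that amyloid PET exists at Amsterdam only.

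**Analysis of those data.** Statistical analysis assigns Pearson or Spearman correlation to the comparison of tears, blood, CSF and PET, and PET enters as a continuous SUVr.

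**The concern.** The article's Background keeps the concepts apart. It says that etiology is determined with biomarkers, sorts these into amyloid, tangles and neurodegeneration, and names CSF or amyloid PET as the tests in current use. An atrophy rating belongs to the third category only. Accuracy against it shows how well a tear marker detects medial temporal atrophy, whatever its cause.

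Two things are at stake. If the markers do well against atrophy, the stated purpose invites readers to take that as diagnostic value for AD, which the analysis cannot establish. If they do poorly against atrophy, the question of amyloid status stays open, and the method named for the Aβ comparison would not answer it in diagnostic terms. The limitations paragraph mentions dropout and incomplete measurements, but not the gap between atrophy and AD.

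**Working it through.** **1. The plan's own figure.** Inputs from Sample size: 95% confidence, expected proportion 0.5, margin 0.10.

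n = z² · p(1 − p) / d² = 1.96² × 0.25 / 0.01 = 96.04, rounded up to 97 per group and 194 in total. The stated 97 + 97 is reproduced. It is sized for accuracy against atrophy, and nothing here calls for changing it.

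**2. Outcome and method side by side.**

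| Listed outcome | Type of reference | Method in Statistical analysis |
|---|---|---|
| Tear tau and atrophy | Binary (MTA cutoff) | ROC, sensitivity, specificity, predictive values, likelihood ratios |
| Tear plus retinal markers and atrophy | Binary (MTA cutoff) | Diagnostic accuracy of the combination |
| Aβ and tau levels in tear, blood, CSF | Continuous | Pearson or Spearman correlation |
| Tear Aβ and Aβ positivity by PET or CSF | Binary (PET read, local CSF cut-offs) | Only correlation of levels is named, with PET as SUVr |

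The last row does not match. A Pearson coefficient is unchanged when either variable is shifted or rescaled, and a Spearman coefficient uses ranks only. Neither involves a threshold on the tear marker or a positive/negative status, so neither yields agreement, sensitivity or specificity against Aβ positivity.

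**3. What ROC against Aβ status would cost in precision.** The worst-case 95% margin for sensitivity is 1.96 × √(0.25 / n₊), where n₊ is the number of Aβ-positive participants with a result. The article does not give n₊, so the values below are assumptions:

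- n₊ = 25: 1.96 × √(0.25/25) = 19.6%
- n₊ = 50: 1.96 × √(0.25/50) = 13.9%
- n₊ = 75: 1.96 × √(0.25/75) = 11.3%
- n₊ = 100: 1.96 × √(0.25/100) = 9.8%, the margin at the planned size of each atrophy group

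Specificity follows the same formula with the number of Aβ-negative participants.

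**4. Composition of the reference-positive group, as context only.** With 100 positives and 50 AD dementia patients in the whole study, at least 100 − 50 = 50 positives (50%) carry no AD dementia diagnosis. With the required 97 positives it is (97 − 50)/97 = 48.5%. If only 90%, 80% or 70% of the AD dementia patients are MTA-positive (assumed), 45, 40 or 35 of them count among the 100 positives, and the share rises to 55%, 60% or 65%. This shows that the reference is not a proxy for the clinical label. It says nothing about how many positives have AD pathology.

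**The case against.** The strongest reply is that the article does not misstate its primary aim. Wherever that aim is set out, it is labelled as neurodegeneration or atrophy. The sentence in the Discussion concerns the study's results in general, says only that they will inform the question, and belongs to a programme that includes an amyloid outcome. The restriction of PET to one centre is disclosed. A condensed article may also leave the method for a secondary outcome to the full protocol or analysis plan.

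Much of this stands. No error in the primary reference, sample size or primary analysis is shown. That a future paper would report the atrophy result as an AD result would be a prediction, not something the document says.

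Two stronger readings are tempting and are not supported:

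- **That no binary AD-specific comparison is planned.** Outcome measures lists one, and note c to Table 3 defines the binary status. The gap lies in the method named for it.
- **That at least half of the reference positives do not have AD.** The count is of participants without an AD dementia diagnosis. Participants with MCI or SCD may have AD pathology. The inclusion criteria require amyloid status in no group, including AD dementia, which is diagnosed on clinical criteria. The 100/100 split is also a target, and fewer positives would lower the bound.

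The reply does not remove the mismatch. The article does name a method for the tear, CSF and PET comparison, and that method does not fit the binary outcome listed. The only accuracy figures it describes are against atrophy, while its stated purpose is AD diagnosis.

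**Conclusion.** The point holds as one of scope and method. The accuracy figures described in the article can support a conclusion about medial temporal atrophy, but not by themselves one about screening for or diagnosing AD. The outcome that could carry an AD statement is listed and has a binary reference, but is paired with correlation of levels, which cannot express diagnostic agreement.

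This rests on the article's own text and needs no assumed figure. The size of the effect on any reported sensitivity or specificity cannot be computed, because the documents give neither the Aβ status of the MTA-positive participants nor the subset size. An unshown analysis plan might already contain an ROC analysis against Aβ status. In that case the method part is settled, and only the wording of the conclusion remains to be aligned. It deserves correction before results are reported, but does not threaten the primary analysis.

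**What to change.** 1. Keep the primary reference and the sample size.
2. In Statistical analysis, assign to the listed Aβ-positivity outcome an ROC analysis of the tear Aβ markers, with sensitivity, specificity and 95% confidence intervals, in the participants with CSF or PET. Correlation can stay for the comparison of levels.
3. Report that analysis by site, because PET is available at one centre only and CSF cut-offs are local. State the numbers of Aβ-positive and Aβ-negative participants.
4. Word the primary conclusion as detection of medial temporal atrophy, and let any AD-diagnosis statement rest on the Aβ-positivity analysis. Add to the limitations that the atrophy rating is not specific to AD.

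**Cost.** Wording changes and one further analysis of data already planned; no new participants or measurements. The headline claim becomes narrower and the intervals wider: about 14% worst-case margin at an assumed 50 Aβ-positive participants, and about 20% per site if those were split 25 and 25.

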### Study status

Recruitment of participants is ongoing. This started on the 24th of March 2021 and is expected to be completed by December 2023, after which participants will return for follow-up visits after 12 and 24 months. The latest version of the study protocol is version 2.0 (date: 16-05-2022).

## Data Availability

Not applicable.

## Abbreviations

AD: Alzheimer’s disease
ATN: Amyloid/Tau/Neurodegeneration
Amsterdam UMC: Amsterdam University Medical Center
Aβ: Amyloid-beta
CSF: Cerebral spinal fluid
CT: Computed tomography
ETDRS: Early treatment diabetic retinopathy study
GCP: Good clinical practice
NFT: Neurofibrillary tangles
NPA: Neuropsychological assessment
Maastricht UMC+: Maastricht University Medical Center
MCI: Mild cognitive impairment
MPOD: Macular pigment optical density
MRI: Magnetic resonance imaging
MTA: Medial temporal lobe atrophy
NIA-AA: National Institute on Ageing-Alzheimer’s Association
OCT: Optical coherence tomography
PET: Positron emission tomography
p-tau: Phosphorylated-tau
RNFL: Retinal nerve fiber layer
ROC: Receiver operating characteristic
SCD: Subjective cognitive decline
t-tau: Total-tau
